## 8.0 STATISTICAL ANALYSES - IMPLEMENTATION

### 8.1 Primary Outcome - Implementation

#### Reach (proportion of patients)

Reach will be measured by the proportion of patients completing one or more ( $\geq 1$ ) cPRO assessments among those eligible for cPRO. This analysis will be a clinic-level analysis analyzed under a cross-sectional design and will only include clinics in the 6 clusters that were randomized. We will calculate reach using 1-month sampling periods within each clinic (as less than 100 individuals in a clinic would be too small for a per-month analysis, our back up will be a 2-month sampling period rather than a 1-month sampling period). The outcome variable will be defined as the proportion of participants who complete a cPRO assessment among those who are eligible within the clinic and the 1-month period. Thus, each month and clinic will have a single data point expressed as a proportion of eligible individuals reached. There are approximately 30 clinics (median of 5 clinics per cluster) and 42 monthly reach proportions will be calculated for each clinic; thus we anticipate 1260 data points for the primary outcome variable. We will use the nlme package in R to perform generalized least squares linear regression modeling with an exposure indicator variable for post-I v. pre-I [referent] entry into the study as the primary predictor of interest. An autoregressive structure will be specified for the correlation structure among the linear model residuals resulting from the repeated measurements of reach within clinic; a lag 1 model will be specified, but model fit under this and other correlation structure specifications will be evaluated according to AIC and BIC. In the generalized least squares setting, the within-clinic repeated measures observation structure is used to define the structure of the covariance matrix. The degrees of freedom is thus the number of calculated proportions calculated for all 1-month intervals and all clinics, less the number of model parameters, including those specified in the covariance matrix. We will perform analyses using an identity link for the outcome variable to estimate risk differences on the raw proportions. In addition, we will log-transform the outcomes to estimate relative risk ratios. We will use clinic-level covariate adjustment for: 1) cluster; 2) time (categorical variable for quarter); 3) number of 1.0 FTE equivalent oncologists per clinic; 4) number of unique patients per clinic; and 5) type of cancer care clinic (e.g., medical oncology, surgical oncology). In sensitivity analyses, we will use weights in the generalized least squares model based on the number of unique eligible patients per clinic. Restricted maximum likelihood (REML) will be used for model parameter estimation as it produces unbiased estimates of the variance and covariance parameters. The primary predictor of interest will be post-I v. pre-I entry into the study, i.e. whether the individual became eligible for cPRO during the pre-I or post-I phase at their site. This clinic-level analysis was chosen as we hypothesize that the impact of the implementation strategy will vary by clinic due to clinic size (clinicians and patients). We will also test for cluster\*treatment and time\*treatment effects to test for a lagged/delayed effect of the exposure, and clinic effects within clusters, in the overall model. Rather than including an a priori transition period, we will conduct a sensitivity analysis around the crossover point in two 1-month increments.

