
## 8.2 Secondary Outcomes - Implementation

### Reach (proportion of patients)

Secondary reach outcomes will be measured as the proportion of patients enrolled in the patient cPRO portal among those eligible and the proportion of patients who are referred for appropriate services from among those that trigger an alert in cPRO. Similar to the primary reach outcome, these proportions will be defined at the clinic level for each 1-month period. The analytic framework for these clinic-level outcomes will be the same as what is described for the primary reach outcome (Section 8.1).

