### Adoption (provider-level)

Adoption by providers will be measured by the proportion of clinicians within a clinic who refer  $\geq 1$  patient who trigger an alert for services, using a cPRO dot phrase, within each 1-month period. The analytic framework for these clinic-level outcomes will be the same as what is described for the primary reach outcome, but with the proportion outcome defined at the provider level (Section 8.1). We will perform a cluster-level analysis if there are fewer than 20 clinicians in any one clinic.

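### The log-transformed relative-risk analysis in SAP 8.1 and 8.2 has no rule for zero proportions, so wherever zeros occur the ratio depends on how they are patched

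*Combined protocol and SAP*

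**What the plan says.** SAP Section 8.1 makes the clinic-month the unit of analysis: "each month and clinic will have a single data point expressed as a proportion of eligible individuals reached". The model is a linear GLS with an autoregressive residual structure within clinic. Two scales are planned. The first is the difference scale: "We will perform analyses using an identity link for the outcome variable to estimate risk differences on the raw proportions". The second is introduced as an addition: "we will log-transform the outcomes to estimate relative risk ratios".

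Section 8.2 applies this to two further reach outcomes, enrolment in the portal and referral among patients who trigger an alert: "The analytic framework for these clinic-level outcomes will be the same as what is described for the primary reach outcome". Provider adoption is the "proportion of clinicians within a clinic who refer" at least one alert-triggering patient with a cPRO dot phrase in the month, and it takes the same framework.

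Two rules limit small denominators. For primary reach, the back-up is a two-month period, "as less than 100 individuals in a clinic would be too small for a per-month analysis". For provider adoption, the analysis moves to cluster level if any clinic has fewer than 20 clinicians. Neither rule says what happens to a proportion of zero. The multiple imputation in Section 9.1 is described for the effectiveness PROs, and a zero is an observed value rather than a missing one.

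**The concern.** A clinic-month with an eligible denominator but no completions, referrals or adopting clinicians has a proportion of zero, and its logarithm does not exist. The analyst must then drop the cell, replace the zero by some constant, or change the model. The SAP names none of these.

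The choice matters if zeros fall unevenly between the phases, which they will if the rate rises after implementation. Dropping zeros discards the lowest observations, more of them from the pre-implementation side. A very small constant turns each zero into an extreme negative value and stretches the contrast. What is at stake is the relative risk reported for the primary implementation outcome and for the secondary outcomes that inherit the method.

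**Working it through.** **The plan's own figure.** Section 8.1 states: "There are approximately 30 clinics (median of 5 clinics per cluster) and 42 monthly reach proportions will be calculated for each clinic", and "thus we anticipate 1260 data points for the primary outcome variable". Figure 1 of the SAP shows 14 quarters; 14 × 3 = 42 months, and 30 × 42 = 1260. The figure reproduces. The SAP gives no expected rate or count of zeros.

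**Plausible cell sizes.** SAP Section 6.0 projects over 18,000 patients a year, about two thirds (12,000) meeting the criteria. Section 3.0 counts 32 clinics. If 12,000 is read as an annual figure and each patient counts in only one month of the year, 12,000 / 32 / 12 ≈ 31 per clinic-month, or about 62 per two months. With 18,000 the averages are about 47 and 94. If each of the 12,000 counts in four months, the average is 125. Visit frequency is my assumption. Clinics differ in size, and Section 7.1 removes consented patients, so cells below these averages will exist. After the two-month back-up, a cell of 31 is a clinic at half the lowest of these averages.

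For provider adoption no clinician counts are given. A cluster of 5 clinics with 10 clinicians each (assumed) has a cell of 50.

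**Method.** P(zero) = (1 − p)^n. The quantity a log-transformed model targets is exp(E[log p̂ post] − E[log p̂ pre]), with p̂ binomial, computed exactly under each zero rule. The true ratio is set at 2.0.

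Example, n = 50, 5% to 10%: P(zero) pre = 0.95^50 = 7.7%.
- Zeros dropped: expected logs −3.059 and −2.399; exp(0.660) = 1.93.
- Zeros set to 0.001: −3.355 and −2.423; exp(0.932) = 2.54.

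| n per cell | pre to post | zeros, pre | drop | 0.5/n | 0.001 |
|---|---|---|---|---|---|
| 100 | 10% to 20% | under 0.01% | 2.06 | 2.06 | 2.06 |
| 100 | 5% to 10% | 0.6% | 2.11 | 2.13 | 2.15 |
| 100 | 2% to 4% | 13.3% | 1.80 | 2.09 | 2.51 |
| 62 | 5% to 10% | 4.2% | 2.03 | 2.17 | 2.36 |
| 50 | 5% to 10% | 7.7% | 1.93 | 2.15 | 2.54 |
| 31 | 5% to 10% | 20.4% | 1.65 | 1.98 | 3.14 |
| 20 | 5% to 10% | 35.8% | 1.41 | 1.73 | 3.71 |

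The 2.06 in the first row is not a zero problem; it is the small shift from averaging logs rather than proportions.

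**Check in the planned design.** A simulation used 6 clusters × 5 clinics × 42 months, the Figure 1 schedule, cluster and quarter effects and AR(1) GLS on log proportions. The true ratio was 1.5, the clinic SD 0.3 on the log scale (both assumed), with 200 replicates.

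| n, baseline | zeros overall | drop | 0.5/n | 0.001 | log-link model |
|---|---|---|---|---|---|
| 100, 10% | 0.03% | 1.53 | 1.53 | 1.53 | 1.50 |
| 100, 2% | 10.2% | 1.35 | 1.50 | 1.73 | 1.50 |
| 20, 5% | 28.7% | 1.19 | 1.32 | 2.06 | 1.46 |

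The log-link column is a Poisson model on counts with an offset (60 replicates). Denominators were equal across cells, so in this check it gives the same point estimate as a log-link model on equally weighted proportions. It needs no zero rule.

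**The case against.** The strongest reply is that the plan already guards against small cells and that the ratio is an addition. Much of this stands.

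- The risk difference on raw proportions is listed first and is defined at zero. Nothing here touches it.
- The two-month back-up and the cluster-level switch reduce zeros. An example with ten clinicians in a clinic-month would describe a cell that the plan does not analyse at clinic level. At 50 clinicians, zeros fall to 0.5% at 10% adoption, though they remain at 7.7% at 5%.
- For primary reach with 100 or more patients per cell and reach of about 10% or higher, zeros are negligible and the patch is irrelevant.

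The safeguards reduce zeros without excluding them. Two months doubles the window but guarantees no minimum. A cluster can hold a single clinic, because SAP Section 3.0 gives a range of 1 to 9. Referral has no minimum for its own denominator, which is only the patients who trigger an alert.

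A reader might infer three stronger things that the documents do not support. One is that zeros will be common, especially before implementation. No baseline rates are given, and cPRO was already live system-wide from March 2018 (SAP Section 2.0), with in-clinic completion offered (Protocol Section 8.0). Another is that provider adoption is the worst case. That outcome has its own fallback, and referral may be as exposed. The third is that any small constant inflates the ratio. In the tables 0.5/n lands on either side of the truth.

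**Conclusion.** The gap is real and confined to the ratio estimates. Section 8.1 specifies a transform that is undefined at an attainable value, Section 8.2 inherits it, and no zero rule is given. Where zeros are common, dropping them pulls the ratio toward 1 and very small constants such as 0.001 inflate it. The effect of 0.5/n varies in direction.

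The size depends on assumed rates and cell sizes. It is nil at 100 per cell and 10%, slight at 100 and 5%, and material at 100 and 2%. At 5% it is also material at 50 per cell (1.93 to 2.54 for a true 2.0) and at 31 per cell (1.65 to 3.14). It would go too far to conclude that the primary implementation result as a whole is unreliable, because the difference-scale analysis does not depend on how zeros are treated. The change should be made before the data are analysed.

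**What to change.** In SAP 8.1 and 8.2, replace the log-transform for the ratio estimates with a log-link mean model fitted to the untransformed proportions. A quasi-Poisson GEE would do, or a nonlinear GLS with an exponential mean, which the nlme package already named can fit. Keep the same covariates, weight clinic-months equally in the main analysis as the plan does now, and allow for within-clinic correlation. Zero cells then enter as observed.

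Put the denominator-weighted version, counts with a log-denominator offset, with the weighted sensitivity analysis that Section 8.1 already plans. Making it the main ratio analysis would move the estimate from clinic-equal to patient-weighted. Also report the number of zero cells by phase for each outcome.

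The cost is SAP wording, a different model call and possible convergence problems. SAP Section 1.0 says that SAP changes need no protocol amendment.

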### 3.0 STUDY DESIGN

#### Implementation Study

A schematic of the study design that illustrates the test of the implementation strategy package is depicted in Figure 1. All clusters will begin with a 6-month pre-I period of data collection. We will use a stepped-wedge trial design comprising seven total clusters. Clusters are the unit of randomization. We will use non-random assignment of the first cluster in the sequence, which was based on readiness to start on our proposed time table, followed by simple randomization of the remaining six clusters to the time of transition from pre-I to post-I. The seven clusters contain 32 clinics (1-9 clinics per cluster). The clinics comprising each of the clusters largely follow naturally occurring administrative structures within the health system (e.g., they share operational leadership). Possible times of transition from pre-I to post-I will follow a quarterly schedule. This will allow within- and between-site evaluation of system-level changes due to prospective introduction of implementation strategies in the observational group of patients completing cPRO assessments and being triaged and referred for relevant clinical services based on their assessment results, under UC. Importantly, the majority of implementation strategies within the package begin immediately prior to or at the point of each cluster's transition from pre-I to post-I.

|           | Year 3 |       |        |        | Year 4 |        |        |        | Year 5 |        |        |        | Year 6 |        |    |    |
|-----------|--------|-------|--------|--------|--------|--------|--------|--------|--------|--------|--------|--------|--------|--------|----|----|
|           | Q1     | Q2    | Q3     | Q4     | Q1     | Q2     | Q3     | Q4     | Q1     | Q2     | Q3     | Q4     | Q1     | Q2     | Q3 | Q4 |
| Cluster 1 | pre-I  | pre-I | post-I | post-I | post-I | post-I | post-I | post-I | post-I | post-I | post-I | post-I | post-I | post-I |    |    |
| Cluster 2 | pre-I  | pre-I | pre-I  | post-I | post-I | post-I | post-I | post-I | post-I | post-I | post-I | post-I | post-I | post-I |    |    |
| Cluster 3 | pre-I  | pre-I | pre-I  | pre-I  | post-I | post-I | post-I | post-I | post-I | post-I | post-I | post-I | post-I | post-I |    |    |
| Cluster 4 | pre-I  | pre-I | pre-I  | pre-I  | pre-I  | post-I | post-I | post-I | post-I | post-I | post-I | post-I | post-I | post-I |    |    |

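### SAP 8.1's primary reach model has no clinic intercept, so if the default AR(1) structure is kept it can absorb lasting clinic differences and lose precision

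*Combined protocol and SAP*

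**What the plan says.** SAP 8.1 defines the outcome as one reach proportion per clinic per month and restricts the analysis to the six randomised clusters. On the model it says: "We will use the nlme package in R to perform generalized least squares linear regression modeling". On covariates: "We will use clinic-level covariate adjustment for: 1) cluster; 2) time (categorical variable for quarter". The remaining covariates are oncologist FTE, patient count and clinic type. No fixed or random clinic term is listed.

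On the residual structure: "a lag 1 model will be specified, but model fit under this and other correlation structure specifications will be evaluated according to AIC and BIC". The candidate structures are not named, and no rule says whether the comparison changes the primary model. Later in the same section, alongside interaction tests, the SAP plans to test for an effect of clinic: "and clinic effects within clusters, in the overall model". It does not say what follows if that test is positive.

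SAP 3.0 gives each clinic a baseline of its own: "All clusters will begin with a 6-month pre-I period of data collection". Section 8.2 applies the 8.1 framework to the secondary reach outcomes and to provider adoption.

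**The concern.** Clinics that share a cluster will probably differ in reach in a lasting way. A cluster term cannot represent that. The only other place for it in the stated model, beyond FTE, size and clinic type, is the residual correlation. AR(1) correlation decays with lag, whereas a constant clinic level gives correlation that does not decay. The fit compromises by raising the lag-1 parameter. A high parameter makes generalised least squares behave more like month-to-month differencing, so the effect is judged mainly from months close to crossover and the rest of each clinic's pre-I record counts for little.

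At stake is the precision of the primary implementation result, and of the 8.2 outcomes that use the same framework.

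**Working it through.** **The plan's own figure.** SAP Figure 1 shows 14 quarters with data: 14 × 3 = 42 months. About 30 clinics × 42 months = 1260 points, as 8.1 states. Clusters 2-7 cross over after 9, 12, 15, 18, 21 and 24 months, so each clinic has 9 to 24 pre-I values. The documents give no standard error, power or variance component for reach, so no precision figure can be reproduced.

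**Assumed inputs.** Clinic SD τ = 0.05 or 0.10 (what remains after FTE, size and clinic type, which were not modelled); monthly SD σ = 0.05; serial correlation φ of the monthly noise from 0 to 0.8; five clinics in each of six clusters. The ratios depend only on τ/σ and φ.

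**Mechanism.** With a lasting clinic level the within-clinic correlation at lag k is (τ² + σ²φᵏ)/(τ² + σ²). For τ = 0.10 and φ = 0 this is 0.0100/0.0125 = 0.80 at every lag. The best-fitting AR(1) parameter is 0.77, which implies 0.77¹² ≈ 0.04 at lag 12.

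**Standard errors.** X holds post-I, quarter and cluster (or clinic) terms. V is the working AR(1) matrix at its REML-optimal parameter and Σ is the true covariance. The true variance is the post-I element of (X′V⁻¹X)⁻¹ X′V⁻¹ΣV⁻¹X (X′V⁻¹X)⁻¹.

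| φ | Fitted AR(1), τ = 0.10 | True SE, stated model | True SE, clinic terms + AR(1) | Ratio, τ = 0.10 | Ratio, τ = 0.05 |
|---|---|---|---|---|---|
| 0 | 0.77 | 0.0123 | 0.0060 | 2.0 | 1.3 |
| 0.3 | 0.84 | 0.0112 | 0.0074 | 1.5 | 1.2 |
| 0.6 | 0.91 | 0.0089 | 0.0078 | 1.14 | 1.07 |
| 0.8 | 0.96 | 0.0064 | 0.0063 | 1.02 | 1.01 |

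At τ = 0.025 the ratio is at most 1.02. Cluster sizes of 1, 3, 5, 5, 7 and 9 clinics give almost the same ratios. Two hundred simulated trials at τ = 0.10, φ = 0 gave an empirical SE of 0.0124 against 0.0055.

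**Power for an assumed 3-point gain**, using the model-based SE and two-sided 5%: Φ(0.03/SE − 1.96).
- φ = 0, τ = 0.10: SE 0.0139 gives 0.58; SE 0.0060 gives over 0.99.
- φ = 0.6, τ = 0.10: SE 0.0090 gives 0.92; SE 0.0078 gives 0.97.

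**Would the AIC/BIC step repair it (τ = 0.10)?**
- φ = 0: compound symmetry beats AR(1) (REML log-likelihood 3607 against 3314) and restores SE 0.0060.
- φ = 0.3: compound symmetry again beats AR(1) (3623 against 3509), but its model SE is 0.0060 against a true 0.0077. Since 1.96 × 0.0060/0.0077 = 1.53, a nominal 5% test has type I error of about 13%.
- φ = 0.3, ARMA(1,1): it fits better still (3636), with model SE 0.0069 against a true 0.0078. Since 1.96 × 0.0069/0.0078 = 1.73, type I error is about 8%.
- φ = 0.3, clinic intercept plus AR(1): it fits best, about 40 log-likelihood units above ARMA(1,1), and its model and true SE agree at 0.0074.

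**With noise shared by clinics in the same cluster and quarter (assumed SD 0.02; τ = 0.10, φ = 0).**
- Stated model: model SE 0.0142, true 0.0175; 1.96 × 0.0142/0.0175 = 1.59, type I error about 11%.
- Clinic terms: model SE 0.0068, true 0.0111; 1.96 × 0.0068/0.0111 = 1.20, type I error about 23%.

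Clinic terms still give the smaller true SE here, but their model-based SE is the more misleading of the two.

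**The case against.** The strongest reply is that 8.1 already allows for this. Compound symmetry within clinic is, for non-negative correlation, the same marginal model as a clinic random intercept, and the AIC/BIC step would choose it over AR(1) by a wide margin in the case where the loss is greatest. If the best of AR(1), compound symmetry and ARMA(1,1) became the primary model, the true SE would be 0.0060 against 0.0060 at φ = 0, 0.0078-0.0079 against 0.0074 at φ = 0.3, and 0.0084-0.0086 against 0.0078 at φ = 0.6. The remaining loss is then about 11% at most. Section 8.1 also plans a test of clinic effects.

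Much of this stands. A reader might infer that AR(1) is bound to absorb clinic differences and that precision will be much lower. The documents do not support that, because they provide for other structures and give no variance figures. Two gaps remain. Neither check is said to decide the primary model, so the choice is left until the data are seen. And at φ = 0.3 the likely winners without a clinic intercept understate the standard error, so a loss of precision is exchanged for excess false positives.

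It is also fair to object that clinic intercepts alone are not a safe remedy. The cluster-quarter calculation bears this out, and the fix below takes it into account.

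**Conclusion.** The point holds as a conditional loss of efficiency. If AR(1) is kept without a clinic intercept, the true standard error is about 1.3-2.0 times what it could be with serially independent monthly noise, 1.2-1.5 times at serial correlation 0.3, and about 1.1 times at 0.6. Above that, or where FTE, size and clinic type explain most clinic differences, the loss is negligible. These sizes rest on the assumed clinic SD of 0.05-0.10 and monthly SD of 0.05. Pilot or pre-I reach data could replace those values.

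A reader might also infer that the package effect is biased. It is not: all clinics in a cluster cross over together, so with balanced data and a fixed correlation, clinic terms leave the estimate unchanged. The loss comes only through the inflated autoregressive parameter.

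The SAP should be changed because this is the primary implementation outcome, the model choice is open, and a clinic intercept with AR(1) had the smallest or equal-smallest true SE in every scenario examined.

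**What to change.** In SAP 8.1, pre-specify a clinic random intercept together with AR(1) residuals (for example `lme` in the nlme package already named), keeping cluster, quarter, the exposure indicator and the listed clinic covariates. Carry this to 8.2. Clinic fixed effects are an alternative, but they contain cluster, and any clinic covariate that is constant over time then drops out. If AIC/BIC is to retain a role, state whether it decides the primary model and include the clinic-intercept-plus-AR(1) structure among the candidates.

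In the same amendment, base inference on the cluster, for example with a randomisation-based test or a cluster-robust variance with small-sample correction. This must accompany the change: if outcomes are correlated within cluster-quarter, the clinic-intercept model's own SE is too small, and adopting it alone would raise type I error.

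Cost: one extra variance parameter (or about 30 − 6 = 24 further fixed effects against 1260 points), a short change to text and code, and the companion inference step.

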## 4.0 STUDY COHORT

### Participant Inclusion Criteria – Implementation

To be eligible for the stepped wedge component of the NU IMPACT study to evaluate implementation outcomes, individuals must meet the following criteria:

- Cancer diagnosis in medical record (ICD-9/ICD-10 code on problem list or encounter diagnosis)
- Visit to the clinic during study period
- Still in care at NMHC (e.g., not deceased, care terminated, etc.)

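### The primary reach model defines exposure by when a patient became eligible rather than by the clinic's phase in that month, and has no term for time since crossover, so a slowly building effect would be heavily attenuated

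*Combined protocol and SAP*

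**What the plan says.** SAP 8.1 specifies a clinic-level analysis, "analyzed under a cross-sectional design and will only include clinics in the 6 clusters that were randomized". In it, "each month and clinic will have a single data point expressed as a proportion of eligible individuals reached", with the proportion taken "among those who are eligible within the clinic and the 1-month period". The model has "an exposure indicator variable for post-I v. pre-I [referent] entry into the study as the primary predictor of interest", and the section later explains that predictor as "whether the individual became eligible for cPRO during the pre-I or post-I phase at their site". Adjustment is for cluster, calendar quarter (categorical) and three clinic descriptors. Residuals within a clinic follow a lag-1 autoregressive structure; no value of the correlation is given.

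For a delayed effect, 8.1 adds cluster-by-treatment and time-by-treatment "effects to test for a lagged/delayed effect of the exposure". The main model has no transition period; instead, "we will conduct a sensitivity analysis around the crossover point in two 1-month increments". SAP 4.0 admits patients to the implementation analysis on, among other things, "Visit to the clinic during study period". The SAP does not say whether a patient who attends in several months counts in each of them. SAP 8.2 applies the same framework to the secondary reach outcomes and to provider adoption.

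**The concern.** There are two separate problems.

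First, the predictor does not fit the data row. A row is a clinic-month; the phase at first eligibility belongs to a patient. In a clinic that has crossed over, patients who first became eligible before and after crossover attend side by side, and all of them attend a clinic that runs the package. One row cannot carry a 0/1 code that differs between the patients in it, and coding the earlier entrants as pre-I would put exposed attendance in the reference group.

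Second, a delayed effect runs on time since crossover, which differs between clusters at any calendar date. Calendar quarter is the only time variable that 8.1 defines, so the interaction uses the wrong clock. If the effect builds up, a single constant coefficient with cluster and quarter effects partly compares newly crossed clusters with clusters whose effect is still growing, and the quarter effects absorb much of that growth.

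At stake is the primary implementation estimate: a package that works, but slowly, could be reported as having little effect.

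**Working it through.** **Inputs.** From SAP 3.0, Figure 1: 14 quarters (42 months); the six randomized clusters (2 to 7) enter post-I in quarters 4, 5, 6, 7, 8 and 9. From SAP 8.1: about 30 clinics, cluster and quarter effects, AR(1) residuals. Assumed, because the documents give no values: the AR(1) correlation, patient turnover and the shape of the effect. Clinics within a cluster are treated as alike and the clinic descriptors are left out.

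**1. The plan's own count.** 30 clinics × 42 months = 1260, as the SAP states. That is one row per clinic-month.

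**2. Could each patient be counted once?** If so, phase at entry equals the phase of the clinic-month and the first problem disappears. The SAP's figures make this unlikely. About 12,000 patients (SAP 6.0) / 1260 rows = 9.5 per row. Even with all 18,000 annual patients new in each of 3.5 years, 18,000 × 3.5 / 1260 = 50. SAP 8.1 treats fewer than 100 people in a clinic as too few for monthly analysis. Protocol 8.0 also sends cPRO before scheduled oncology visits, so repeat attendance is expected.

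**3. Immediate effect under each coding** (share of the true effect that is estimated). Assumption for patient-entry codings: 20–90% of patients seen at crossover are carried over from pre-I, decaying with a time constant of 3–24 months; working independence.
- Phase of the clinic-month, or each patient counted once: 1.00
- One row, coded by the majority of its patients (90% carry-over): −0.27 to 0.61
- One row, exposure = share of post-I entrants: 0.93 to 1.63
- Two rows per post-I clinic-month, weighted by share: 0.04 to 0.54; unweighted: 0.12

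**4. Lag test.** In quarters 1–3 all six clusters are pre-I; in quarters 9–14 all are post-I. The quarter-by-treatment term is estimable only in quarters 4–8, which is 14 − 3 − 6 = 5. For a 12-month build at correlation 0.5 it gives 0.02, 0.10, 0.18, 0.26 and 0.29 of a plateau of 1. Cluster by treatment falls from 0.33 to 0.05. Both signal a trend; neither recovers its size.

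**5. Constant effect with clinic-phase coding.** Let the effect in the k-th post-I month be min(k/L, 1). The expected coefficient is the exposure element of (XᵀWX)⁻¹XᵀWy, with W the inverse AR(1) matrix within cluster. Post-I months per cluster are 33, 30, 27, 24, 21 and 18, total 153, so the true post-I mean is 1 − 6 × ((L − 1)/2)/153.

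| Build-up L | True post-I mean | Correlation 0 | 0.5 | 0.8 |
|---|---|---|---|---|
| Immediate | 1.00 | 1.00 | 1.00 | 1.00 |
| 3 months | 1 − 6/153 = 0.96 | 0.82 | 0.62 | 0.40 |
| 6 months | 1 − 15/153 = 0.90 | 0.58 | 0.40 | 0.20 |
| 12 months | 1 − 33/153 = 0.78 | 0.25 | 0.17 | 0.08 |

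For a 10-point plateau, a 6-month build is estimated as 5.8 to 2.0 points (true mean 9.0) and a 12-month build as 2.5 to 0.8 (true mean 7.8).

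**6. Crossover sensitivity analysis.** The SAP does not say how the two months are handled. If the first two post-I months are dropped, the coefficient is 1.00 for a 3-month build, 0.79 to 0.59 for 6 months and 0.39 to 0.32 for 12 months, at correlation 0 to 0.8.

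**7. Time since crossover modelled.** Monthly indicators with cluster and quarter effects are full rank on Figure 1 (52 of 52 columns). The mean over months 1–12 equals the truth: 1.00 for an immediate effect, and 0.92, 0.79 and 0.54 for 3-, 6- and 12-month builds. For precision, compare √(aᵀ(XᵀWX)⁻¹a), where a averages the first year, with the same quantity for the constant effect. With quarterly indicators the ratio is 1.39 at correlation 0.5 and 1.79 at 0.8; with monthly indicators it is 1.44 and 2.01. Quarterly indicators smooth over growth within a quarter: for a 6-month build at 0.5 they give (0.32 + 0.70 + 0.84 + 0.88)/4 = 0.685 against a true 0.79.

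**The case against.** The context favours clinic phase as the intended exposure. SAP 8.1 calls the analysis clinic-level and cross-sectional, SAP 3.0 randomizes clusters, and SAP 8.2 uses the same framework for a proportion of clinicians, which no patient's eligibility date could code. The patient-level explanation may be loose wording. This stands as a guide to intent, but 8.1 describes the predictor by entry twice, and a programmer following it would have to choose a rule.

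A reader might infer that the definition, taken literally, erases even a real and immediate effect. Separate rows for pre-I and post-I entrants do give estimates near zero under slow turnover. The documents do not support that reading. Figure 1 has 51 post-I cluster-quarters, so splitting would add 51 × 3 × 5 = 765 rows, making 2025, against the SAP's single data point per clinic-month and its count of 1260. Codings that keep one row range from loss to inflation, and clinic-phase coding loses nothing.

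On delay, SAP 3.0 says that most strategies start at or just before transition, so an early effect is plausible. Working correlations other than lag-1 will be compared by AIC and BIC. The planned interactions would give some sign of a lag, and dropping two months would repair a 3-month build. All of this stands. It does not help with a build of 6 months or more, and 8.1 does not say what follows if an interaction is found.

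**Conclusion.** The concern holds in two parts. The exposure definition is ambiguous: an immediate effect is recovered in full if exposure is the clinic-month's phase, but if patients recur and entry phase is used, the one-row codings give −0.27 to 1.63 of the true effect under assumed turnover. This shows dependence on an unstated rule, not a demonstrated bias in one direction.

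The missing time-since-crossover term matters even with correct coding. At an AR(1) correlation of 0 to 0.8 the constant effect captures 0.82–0.40 of the plateau for a 3-month build, 0.58–0.20 for 6 months and 0.25–0.08 for 12 months, against true post-I means of 0.96, 0.90 and 0.78. The planned checks repair only the 3-month case, and only if the two months are dropped.

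These sizes rest on the Figure 1 schedule, a linear build and assumed correlations. They do not show that the package will appear ineffective: that depends on how fast the effect arrives, which the documents do not say.

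**What to change.** - In SAP 8.1, set exposure to 1 when the clinic is in post-I in that month and 0 otherwise, and delete the patient-entry explanation. Count every patient eligible in that clinic-month, whatever the date of entry, and state that patients may recur across months. This costs nothing.
- Replace the calendar time-by-treatment lag test with indicators for time since crossover, keeping cluster and quarter effects. Pre-specify their average, for example over months 1–12 after crossover, as a key sensitivity analysis reported beside the constant-effect estimate. State that a small constant effect is not to be read as null if the two disagree.
- State whether the two 1-month increments are dropped, recoded or shifted.
- Carry the same definitions into SAP 8.2.

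No new data are needed, and SAP 1.0 says that SAP changes need no protocol amendment. The price is precision: the exposure-time average has a standard error about 1.4 to 1.8 times that of the constant effect with quarterly indicators, and up to about 2 times with monthly ones, which follow a build more faithfully. Whether to make that average the primary estimate is therefore a trade-off for the sponsor.
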